## Sample size calculation

4

Three hundred and ninety‐two participants will be recruited across all sites. This calculation is based on detecting a 20% improvement in the survival rate for extended MACE (a much smaller reduction than a similar intervention in another high risk T2D population^17^) at 24 months from 65.6% (34.4% experience an event) to 78.7% (21.3% experience an event). The 65.6% rate in the control arm at 24 months was extrapolated from two of our previous studies in this population.^11^, ^18^ Assuming 80% power and 5% alpha, a sample size of 372 participants is required. Allowing for a 5% drop out (low because primary outcome will be collected by data linkage) similar to previous work,^14^ the number of participants required increases to 392. The sample size calculation may be proactively refined if any further relevant data emerge in the literature during the study.

## Secondary study aims

5

### Cost effectiveness of MiFoot

5.1

Two health economic analyses will be conducted to assess the cost‐effectiveness of MiFoot: (1) an analysis of economic data collected within the trial; and (2) a long‐term economic modelling analysis (lifetime horizon). Both analyses will take an NHS and personal social services perspective, and the long‐term analysis will discount future costs and quality‐adjusted life years (QALYs) at 3.5% per annum, based on National Institute for Health and Care Excellence (NICE) recommendations.^19^ Both analyses will estimate incremental cost‐effectiveness ratios for study outcomes, including QALYs, comparing the MiFoot intervention to usual care. The long‐term model will be based on our existing health economic model, the School for Public Health Research Type 2 Diabetes Treatment Model (SPHR‐T2DMT).^20^

## Sustainability of MiFoot

6

### Internal feasibility

6.1

An internal feasibility study, designed to evaluate the viability of the study during its initial phases, will be undertaken. This will evaluate the feasibility of recruiting to target in the study. Hence, the stop‐go criteria are based on the first 3 months of recruitment, when recruitment should be 25% complete (i.e. 98 participants). To allow for a slower start, feasibility criteria will be set at 20% of the recruitment target (i.e. 78 participants). Based on the actual number of patients recruited after 3 months compared with the target of 78 participants (red: ≤49; amber: 50–77; green: ≥78), the Data Monitoring and Safety Committee (DMSC) will make a recommendation on how to proceed.

### Adherence and retention

6.2

In order to increase participant engagement by tailoring the intervention to the individual, the different components of the MiFoot intervention are made optional, enabling participants to choose which component or combination of components they want to engage with. The intervention is also theoretically underpinned to support behaviour change and engagement throughout the trial. The physical and psychological challenges of this population were considered during the development phase, and the programme is tailored to address their needs. For example, to encourage adherence to the digital programme, we not only have the educational material and tools for people to set a behavioural goal, but we also include a chat forum to promote peer support. Moreover, additional support is offered to the participants to address low digital literacy. Physical activity is also tailored to participants' needs, accommodating any personal pain, co‐morbidities or mobility limitations. Additionally, a concurrent refinement exercise will run parallel to the intervention wherein participants' experiences will be surveyed after partaking in each component of the intervention and survey responses will be used to make refinements. Adherence and retention, as longer term outcomes, will not form part of the initial stop‐go feasibility criteria.

### Process evaluation

6.3

A mixed‐methods process evaluation, based on the RE‐AIM framework,^21^ will be carried out to investigate individual experiences with the intervention, potential barriers and facilitators to intervention delivery, attendance (including delineation of these factors based on each different element of the intervention), and intervention fidelity.

## Statistical analysis

7

A full statistical plan will be finalised prior to database lock before any unblinded data has been seen by the statistician. The primary analysis will compare the primary outcome (extended MACE at 24 months) between treatment groups using a Cox proportional hazards regression model, assuming assumptions are met. The model will be fitted with time to extended MACE as the outcome and treatment group as the main explanatory variable. The stratification factors (site, age, sex) will be adjusted for, and participants lost to follow‐up will be censored at the last date at which they were known to be event‐free. If any baseline imbalances become evident, these will be investigated using secondary exploratory analyses.

For the event outcomes (renal end points, extended MACE components and all‐cause mortality, amputation), the analysis approach will be a Cox proportional hazards model adjusted for the stratification factors in line with the primary analysis. The questionnaire summary measures, biomedical markers and anthropometric measures will be compared between treatment groups using linear mixed regression models adjusted for time (baseline, 12 and 24 months) and the stratification factors. Missing data for non‐event outcomes will be imputed using multiple imputation where data can be assumed to be missing at random. A sensitivity analysis will be carried out removing any variables with >10% missing data.

Summary measures (number of events or mean change from baseline) by treatment group, effect size, 95% confidence interval and two‐sided *p*‐value will be presented for each of the primary and secondary analyses. Statistical significance will be assessed at the 5% level.

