#### Baseline research data extraction

2.4.3

Routine health data, medical history, all current diagnoses and dates, procedures/surgeries and medications, will be extracted from participants' medical records. Routine biomarker results, as listed in Table 1, that are within 6 months, will be extracted or requested through the GP.

**TABLE 1 dme70028-tbl-0001:** Secondary outcomes, measures and time of measurement during the study.

Secondary outcomes	Measures	Visits		
		Baseline visit, Month 0	Remote, 12‐month follow‐up	Remote, 24‐month follow‐up
Health outcomes	Composite renal end points: End‐stage kidney disease (defined as dialysis, transplantation, or a sustained (>3 months) estimated Glomerular Filtration Rate [eGFR] of <15 mL/min/1.73 m^2^) Doubling of the serum creatinine level Or death from renal causes 3‐Point MACE (non‐fatal myocardial infarction, non‐fatal stroke and cardiovascular death) and components of the extended MACE All‐cause mortality Lower limb major amputation Self reported re‐ulceration		X	X
Patient‐reported outcomes	Using Questionnaires: Distress using Problem Area in Diabetes‐20 (PAID‐20) Self‐efficacy using Diabetes Management Self‐Efficacy Scale‐15 (DMSES‐15) Quality of Life using Diabetes Foot Ulcer Disease (Diabetes Foot Scale‐Short Form [DFS‐SF], generic EuroQoL‐5Dimension‐5Levels [EQ‐5D‐5L]) Depression and anxiety using Hospital Anxiety and Depression Scale (HADS) Health resource use, such as primary care visits, emergency department visits, hospitalisations and medication use using Modular Resource‐Use Measure (ModRUM) Medication adherence using the Morisky Medication Adherence Scale (MMAS‐8) Diet using the Short Form Food Frequency Questionnaire Sleep duration/quality and physical activity volume/intensity measured objectively using wrist worn accelerometers	X	X	X
Biomedical markers	Blood pressure (systolic, diastolic and heart rate) (mmHg, BPM) Low‐density lipoprotein‐cholesterol (LDL‐C) (mmol/L) High‐density lipoprotein‐cholesterol (HDL‐C) (mmol/L) Total cholesterol (TC) (mmol/L) Triglycerides (TG) (mmol/L) Glycated haemoglobin (HbA1c) (% and mmol/mol) Estimated Glomerular Filtration Rate (eGFR) (mL/min/1.73 m2) Urine albumin: creatinine ratio (uACR).	X	X	X
Anthropometric	Weight Body mass index (BMI)	X	X	X

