#### Randomisation

2.4.7

Participants will be randomly allocated 1:1 to the control or intervention arm using an online 24‐h system provided by the Derby Clinical Trials Support Unit (DCTSU). Block randomisation will be stratified by site, sex (men; women) and age (<50; ≥50 years).

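### The primary Cox model adjusts only for site, age and sex; pre-specifying a few prognostic covariates already collected at baseline would add modest power

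*Protocol article*

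**What the plan says.** The Statistical analysis section describes a Cox model for time to extended MACE with treatment group as the main explanatory variable. On covariates it says "The stratification factors (site, age, sex) will be adjusted for" and names no others. On chance imbalance it says "If any baseline imbalances become evident, these will be investigated using secondary exploratory analyses". A full statistical plan is to be finalised before database lock and before the statistician sees unblinded data.

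The Randomisation section stratifies by site, "sex (men; women) and age (<50; ≥50 years").

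The following would be available at baseline:

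- Age is recorded (Baseline measure data collection).
- Cardiovascular history comes from records: "Routine health data, medical history, all current diagnoses and dates, procedures/surgeries and medications, will be extracted" (Baseline research data extraction).
- eGFR is among the Table 1 biomarkers, taken from results within six months or requested through the GP.
- Ulcer status is established for eligibility, since people with a current ulcer and people with one in the past five years may both enter (Inclusion and exclusion criteria).

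**The concern.** The trial admits a mixed-risk population. Current and past ulcers are both eligible, and prior cardiovascular disease is not an exclusion. Randomisation balances neither factor. If age enters the model in the form used for stratification, a single cut at 50 years discards most of the information in the exact age.

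In a Cox model, leaving out a predictor of the event moves the estimated log hazard ratio toward zero with almost no compensating fall in its standard error. Some power is therefore lost. The sample size assumes a large effect, a hazard ratio of about 0.57, so a few points of power at little cost are worth having.

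The imbalance sentence is a lesser matter. It gives no list of variables, no threshold and no model, so which adjusted analyses are run will depend on what the baseline table shows. Under randomisation any imbalance is due to chance. What makes a covariate worth adjusting for is its prognostic strength, and that can be settled in advance.

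**Working it through.** **Inputs from the protocol article.** Sample size calculation: "at 24 months from 65.6% (34.4% experience an event) to 78.7% (21.3% experience an event"); "Assuming 80% power and 5% alpha, a sample size of 372 participants is required"; "Allowing for a 5% drop out", giving 392. Statistical analysis: results are reported with a "95% confidence interval and two‐sided" p-value. Randomisation: allocation is 1:1.

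**Step 1: the plan's own figure.**

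- Implied hazard ratio = ln(0.787) / ln(0.656) = 0.568.
- Freedman events = (1.960 + 0.842)² × [(1 + 0.568) / (1 − 0.568)]² ≈ 104.
- Mean event risk = (0.344 + 0.213) / 2 = 0.2785, and 104 / 0.2785 = 373.4, so 374 participants.
- Two proportions without continuity correction give 366. Both are close to the stated 372.
- 372 / 0.95 = 391.6, so 392.
- Expected events at 372 participants = 372 × 0.2785 = 103.6. Power is 82% by Schoenfeld and 81% by two proportions.

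None of these formulas uses a covariate, so the planned 80% does not depend on prognostic adjustment.

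**Step 2: one combined prognostic score.** The documents give no predictor strengths, so a range is assumed. Event times are exponential with hazard proportional to exp(σZ), Z standard normal, censored at 24 months. The arm-specific hazards are solved so that the overall 24-month risks stay at 34.4% and 21.3%. Each setting has 372 participants and 3,000 runs, with a Monte Carlo standard error of about 0.7 points per estimate.

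| Assumed HR per SD of score | Power without score | Power with score | Gain (points) |
|---|---|---|---|
| 1.35 | 80.5% | 81.7% | 1.2 |
| 1.65 | 80.9% | 84.2% | 3.3 |
| 2.01 | 81.1% | 86.9% | 5.8 |
| 2.72 | 80.6% | 91.5% | 10.9 |

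The last row is an extreme case.

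**Step 3: four separate predictors.** The same planned risks and 372 participants were used, with 3,000 runs per setting. A model with treatment and dichotomised age was compared with one containing treatment, continuous age, prior cardiovascular disease, eGFR and active ulcer.

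| Assumed strength | Prior CVD HR | Age HR per SD | eGFR HR per SD | Active ulcer HR | Power, dichotomised age | Power, all four |
|---|---|---|---|---|---|---|
| Weak | 1.7 | 1.2 | 1.2 | 1.3 | 81% | 82% |
| Moderate | 2.0 | 1.3 | 1.3 | 1.4 | 82% | 85% |
| Strong | 2.5 | 1.5 | 1.4 | 1.5 | 82% | 88% |

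The gains are 1, 3 and 6 points, in line with step 2.

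**Step 4: where the gain comes from.** At a score HR of 2.01 per SD in step 2, the mean estimated treatment hazard ratio moves from 0.567 to 0.540 on adjustment. In companion runs (4,000 per setting) with the conditional hazard ratio held at 0.568, the standard error of the log hazard ratio was 0.201 without the score and 0.202 with it. The gain comes from a larger log hazard ratio, not from a smaller standard error. The adjusted model therefore estimates a more conditional effect.

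**Limits.** Covariates are treated as complete, site effects are not modelled, and the score in step 2 is independent of site, age and sex. Step 3 includes eGFR; without it the gain would be expected to be somewhat smaller.

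**The case against.** The strongest reply is that nothing here is wrong. Adjusting for the stratification factors is correct practice, the covariates are fixed in advance, and further covariates and the coding of age could be settled in the analysis plan, which is not shown. This largely stands and limits the point to a suggested improvement. The point survives because the article does not leave the primary covariates open: it names them, and a better set is available.

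The costs are also real. eGFR depends on routine results and may be missing, while the multiple imputation described covers only non-event outcomes. Including eGFR without a further rule could remove participants from the primary analysis. The hazard ratio changes meaning, although the planned model is already conditional on site, age and sex. The number of sites is not given, so about 104 events will not support a long covariate list. These downsides are small and can be handled.

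Three stronger readings are tempting, and the documents do not support them:

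- *The primary analysis is data-driven.* The imbalance sentence sends such adjustment only to secondary exploratory analyses. The primary model and its type I error are unaffected. What remains is that an unplanned adjusted result might disagree with the primary one.
- *The trial is underpowered without these covariates.* In the companion runs of step 4, the unadjusted model has 74.7% power against 81.3% at a score HR of 2.01 per SD. Those runs let the intervention-arm risk rise above the planned 21.3%. At the risks the protocol states, the unadjusted model keeps about 81%.
- *The age split separates almost nobody, and the omitted factors are known to be strong.* The documents give neither an age distribution nor any predictor hazard ratio. They also do not say whether age enters the model as the split or as a continuous term.

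**Conclusion.** The point holds as missed efficiency. The primary test is valid, 372 and 392 are reproduced, and the stated 80% power is met by a model without further covariates. Pre-specified adjustment would add roughly 1 to 3 points of power for weak to moderate predictors and about 6 for strong ones. The weak case is about the size of the simulation error. The gain rests on assumed predictor strengths, complete covariates and the protocol's own 24-month risks. The exploratory imbalance rule does not endanger the primary result, but a fixed adjusted analysis would be cleaner.

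**What to change.** Before any unblinded data are seen, specify in the statistical analysis plan:

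1. A primary Cox model with treatment, site, sex, continuous age, prior cardiovascular disease or revascularisation (yes/no), and current versus previous ulcer.
2. Baseline eGFR as a further term only if the plan states a rule for missing baseline values that keeps every randomised participant in the analysis.
3. The model with stratification factors only as a sensitivity analysis, so that the less conditional estimate is also reported.
4. Removal of the imbalance-triggered exploratory analysis in favour of this fixed covariate set.

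No new data collection is needed. Continuous age takes the place of the age split, so the model gains two terms, or three with eGFR. The cost is wording in the analysis plan, a simple missing-baseline rule, a somewhat more conditional hazard ratio that the report should describe as such, and restraint on further terms given about 104 expected events and several sites.

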### Follow‐up assessments

3.1

Participants will be followed up for 24 months using the same measures as the baseline visit through questionnaires, accelerometers, routine health data and health outcomes (Tables 1 and 2). There will be no on‐site visits for the 12‐ and 24‐month assessments.

**TABLE 2 dme70028-tbl-0002:** Schedule of procedures.

Procedures	Visits			
	Pre‐screening	Baseline visit, Month 0	Remote, 12‐month follow‐up	Remote, 24‐month follow‐up
Invitation and EOI	XX			
Telephone screening	XX			
Informed consent		XX		
Face to face eligibility screening		XX		
Demographics		XX		
Baseline Research Data Extraction		XX		
SINBAD Score		XX		
Consent		XX		
Inform GP of study participation		XX		
Randomisation		XX		
Anthropometric		XX	XX	XX
Patient‐reported outcomes Questionnaires		XX	XX (±4 weeks)	XX (±4 weeks)
Accelerometer		XX (±4 weeks)	XX (±4 weeks)	XX (±4 weeks)
CGM provision		XX^a^		
ECG		X		
Health outcomes data collection		XX	XX	XX
Biomedical markers		XX	XX	XX
Physical activity screening		X		
Adverse event assessments Safety measures		X	X	X
Process evaluation observations		X		
Process evaluation feedback surveys		X^b^		
Process evaluation questionnaires			X	
Process evaluation interviews				After 24th month

*Note*: X: Intervention arm only; XX: All study participants.

Abbreviations: ECG, electrocardiogram; EOI, expression of interest; GP, general practitioner; SINBAD, ulcer site, ischemia, neuropathy, bacterial infection, area and depth.

^a^
All participants will be offered CGM devices at their baseline appointment; though if they decline at this stage, they can change their mind throughout the trial.

^b^
After each one‐to‐one and group sessions and 4 weeks after the digital programme, collected up to month 9 of the intervention delivery.

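### As written, the mixed model for questionnaire, biomedical and anthropometric outcomes takes baseline as an outcome time with no term separating it from follow-up, which pulls the treatment effect toward zero

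*Protocol article*

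**What the plan says.** All of the text at issue is in the Statistical analysis section of the protocol article.

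- Outcomes and comparison: "The questionnaire summary measures, biomedical markers and anthropometric measures will be compared between treatment groups".
- Model: "linear mixed regression models adjusted for time (baseline, 12 and 24 months) and the stratification factors".
- Reporting: "Summary measures (number of events or mean change from baseline) by treatment group", together with an effect size, a 95% confidence interval and a two-sided p-value.
- Further detail: "A full statistical plan will be finalised prior to database lock". That plan is not shown.

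The Follow-up assessments section confirms repeated measurement: "Participants will be followed up for 24 months using the same measures as the baseline visit". Under Randomisation, participants are "randomly allocated 1:1 to the control or intervention arm".

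**The concern.** The sentence makes baseline one of three levels of the time factor, so baseline values are responses and not covariates. Time has the same role as site, age and sex: a quantity adjusted for. On the ordinary reading the model is treatment + time + stratification factors. Its single treatment coefficient is then a weighted average of the between-arm differences at baseline, 12 and 24 months. Randomisation makes the first of these zero in expectation, so a known zero is averaged into the effect.

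Three consequences follow.

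- The estimate is biased toward zero, and a larger sample does not cure it. The test is still valid when there is no effect at all; the harm is to estimation and power.
- The reported effect would not agree with the between-arm difference in mean change from baseline printed beside it, which in expectation is the full effect.
- No separate 12- or 24-month effect is estimated.

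The outcomes covered include HbA1c, LDL-C, blood pressure, weight, diabetes distress and quality of life. The intervention is meant to work through intensive risk-factor control, so these results will be used to interpret the cardiovascular result. Shrunken estimates could wrongly suggest that the risk factors barely moved.

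**Working it through.** **The plan's own figure.** The only sample size is for the primary outcome: "Assuming 80% power and 5% alpha, a sample size of 372 participants is required". It reproduces with the Freedman log-rank formula:

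- hazard ratio = ln(0.787)/ln(0.656) = 0.568
- events = (1.960 + 0.842)² × (1.568/0.432)² = 103.5
- N = 103.5/(1 − 0.7215) = 371.6, rounded up to 372
- 372/0.95 = 391.6, rounded up to 392

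The figure is sound, and the present point does not touch it. It is used only to set n = 372/2 = 186 per arm below. The article gives no power figure for the continuous outcomes.

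**Assumptions (not in the documents).** True effect d, equal at 12 and 24 months and zero at baseline; complete data; equal variances scaled to 1 SD; within-person correlation ρ.

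**Expected estimate with treatment as a main effect only.** Generalised least squares weights the three visit differences by w = V⁻¹1/(1ᵀV⁻¹1), where V is the within-person correlation matrix. The expected coefficient is w applied to (0, d, d).

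- Exchangeable correlation, any ρ: w = (1/3, 1/3, 1/3), giving 2d/3 = 0.667d.
- AR(1), ρ = 0.5: w = (0.40, 0.20, 0.40), giving 0.60d.
- AR(1), ρ = 0.7: w = (0.435, 0.130, 0.435), giving 0.565d.

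**Power at d = 0.25, exchangeable correlation, two-sided 5%.**

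- Model as written: expected estimate 0.1667; SE = √[(2/186)(1 + 2ρ)/3].
- 24-month contrast with arms constrained equal at baseline: expected estimate 0.25; SE = √[(2/186)(1 − ρ²)].
- Power = Φ(estimate/SE − 1.96). Information ratio = (second z / first z)².

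| ρ | As written: SE, z, power | 24-month contrast: SE, z, power | Information ratio |
|---|---|---|---|
| 0.3 | 0.0757, 2.20, 59.5% | 0.0989, 2.53, 71.5% | 1.3 |
| 0.5 | 0.0847, 1.97, 50.3% | 0.0898, 2.78, 79.5% | 2.0 |
| 0.7 | 0.0927, 1.80, 43.5% | 0.0741, 3.38, 92.2% | 3.5 |

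Higher correlation makes the model as written less powerful and the alternative more powerful: the first wastes the baseline information and the second uses it.

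**Simulation check.** Random-intercept data with 392 participants, d = 0.3, ρ = 0.6, complete, 100 replicates. With treatment as a main effect only, the mean estimate was 0.197 and power about 56%. With a treatment-by-time interaction, the 24-month term averaged 0.299 with power about 92%.

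**Sensitivity of the dilution.** The factor is not fixed.

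- If the 12-month effect is half the 24-month effect, exchangeable correlation gives (0 + 0.5 + 1)/3 = 0.50 of the 24-month effect.
- If follow-up SDs are 1.2 times the baseline SD, with exchangeable correlation and an equal effect at both follow-ups, the factor is 0.53 at ρ = 0.3 and 0.29 at ρ = 0.7.
- With an interaction or a baseline constraint there is no dilution.

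**The case against.** The strongest reply is that the article never says treatment enters as one constant effect. It is a condensed account, it defers to a full plan, and interaction terms and covariance structure are commonly left there. Baseline as an outcome time is not itself an error, since the constrained model recommended here uses it too. Reporting mean change from baseline may even suggest that a treatment-by-time contrast was intended.

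Part of this stands. A reader might infer that the protocol states a constant treatment effect; it does not. That is the natural reading of the sentence, but an interaction is not excluded, and the dilution is conditional on it. The reply does not dispose of the point, though. The article goes beyond silence: it publishes a model form, and following it literally gives the diluted estimate. Mean change from baseline is listed as a by-group summary, separate from the effect size, and does not define the model.

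Two further readings go too far.

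- That every continuous secondary outcome is affected. The sentence does not name the CGM metrics and does not clearly cover the accelerometer measures.
- That the gain from the remedy is 2.1- to 5-fold in information, with power of 90%, 93% and 98%. Those figures belong to one coefficient pooled over both follow-up visits, not to the 24-month contrast proposed here.

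**Conclusion.** The point holds in conditional form. The model sentence gives no term that separates the follow-up treatment effect from the baseline difference. If it is fitted with treatment and time as main effects, the expected loss is about one third of the effect under exchangeable correlation and about 40% to 43% under AR(1) with ρ of 0.5 to 0.7. Other variance patterns or effect profiles can make it larger. These sizes, and the power figures, rest on effect sizes, correlations and complete data assumed here.

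Severity is moderate. Only the named secondary outcomes are affected. The primary Cox analysis, the event-type secondary outcomes and the sample size of 392 are not.

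**What to change.** Amend the model sentence in the Statistical analysis section and carry it into the SAP before database lock. For the questionnaire, biomedical and anthropometric outcomes, specify:

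- a linear mixed model with a common baseline mean in both arms, treatment-by-time terms at 12 and 24 months, unstructured covariance and the stratification factors; or, as an alternative, the 12- and 24-month values as outcomes with the baseline value as covariate;
- the 24-month contrast as the main effect, with the 12-month contrast alongside.

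The amendment should also say whether the accelerometer and CGM measures follow the same model.

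The cost is a sentence or two of text. No new data, visits or participants are needed.
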